1. SUMMARY

The London School of Hygiene & Tropical Medicine (LSHTM) has been engaged by Portland State University (PSU to conduct an independent evaluation to assess the uptake, performance and environmental exposure impact (drinking water and indoor air quality) of a pilot project in Rwanda to distribute water filters and improved cook stoves to 2000 households in 11 districts. The pilot project is designed to provide information on whether to proceed with a large-scale delivery of the intervention in Western Rwanda. The intervention is being implemented by DelAgua Health (DelAgua) in cooperation with the Rwanda Ministry of Health (MoH).

2. BACKGROUND

Environmental contamination at the household level is a major cause of death and disease, particularly among rural populations in low-income countries. Unsafe drinking water, together with poor sanitation and hygiene, account for an estimated 9.1% of the global burden of disease and 6.3% of all deaths. Much of this disease burden is associated with diarrhea, which alone accounts for 21% of deaths in children under 5 years in low-income countries. Indoor air pollution contributes to acute lower respiratory infection (ALRI), the leading cause death in children. These environmental hazards are further aggravated among rural inhabitants of sub-Saharan Africa who are more likely to rely on unsafe water supplies and cook using biomass fuels on inefficient stoves.

Inefficient stoves also present substantial economic, developmental and environmental costs. At the household level, poverty is exacerbated and time spent at school reduced by the burden of collecting up to 50% more fuel for boiling drinking water and cooking. Individuals, households and governments bear the cost of expenditures for seeking treatment of enteric and respiratory infections. Low-efficiency stoves contribute to denuding of forests for fuels, urban air pollution and greenhouse gas emissions.

With a population expected to reach 12 million in 2012, Rwanda is the most densely populated country in Africa. Eighty per cent of the population of Rwanda lives in rural areas and is engaged in agriculture. Despite significant progress over the last decade, 57% of the population is living below the poverty line, 37% of them living in extreme poverty. Annual per capita income increased from US$ 235 to US$ 291 between 2002 and 2008. Morbidity and mortality is still dominated by communicable diseases, which account for more than 90% of visits to health facilities. The most common communicable diseases are malaria, HIV/AIDS, acute respiratory infections, diarrhoeal diseases and tuberculosis.

In an effort to reduce the disease burden in rural Rwanda, decrease poverty associated with expenditures for fuel, and minimize the impact of greenhouse gases from inefficient combustion of biomass, the Rwanda Ministry of Health (MoH) and the Rwanda Environmental Management Authority (REMA) has partnered with DelAgua Health and Development (DelAgua) and Manna Energy (Manna) to design, deploy and evaluate the impact of an project that will deliver and promote the use of advanced water filters and high efficiency cook stoves to serve 3 million people in Western Rwanda. The intervention will be delivered by community health workers (CHWs) under the supervision of the MoH. It will be financed by carbon credits under the United Nations Clean Development Mechanism.

Prior to initiating the full campaign mid 2013, the implementers are undertaking a pilot distribution of 2000 filters and cook stoves. The objective of the pilot is to optimize delivery strategies and ensure that the accompanying promotional activities succeed in yielding high uptake and use of the hardware. The implementers have contracted with PSU to conduct the overall evaluation of the pilot. PSU, in turn, has engaged LSHTM to evaluate certain aspects of the pilot, namely the process for delivering the intervention, uptake and use of the hardware, and the impact of the intervention on drinking water quality and indoor air quality. These will be assessed by undertaking a process evaluation study and a separate randomized control trial (RCT). This protocol concerns only the RCT. Any evaluation of the full-scale roll out of the intervention will be subject to a separate protocol and ethics review.

3. STUDY OBJECTIVES

(i) To asses uptake and use of the intervention by the target population when delivered programmatically, and

(ii) To assess the impact of the intervention on the microbiological quality of household drinking water and air quality near the self-reported cooking area over the 5-month follow-up period.

4. INTERVENTION

The intervention consists of the delivery of advanced microbiological water purifiers and high efficiency cook stoves (described below) and promotion of their correct, consistent use. The intervention is delivered at the community level by CHWs who are engaged by the MoH to provide a variety of health related services to rural villages in Rwanda. The strategy and specific promotional activities for delivering the intervention were developed based on a pre-pilot project among 100 villages by the implementing organizations and approved by the MoH. Following informed consent from participating householders, CHWs will provide the intervention hardware and instructions for use. They will return to each household within 10-20 days following the initial delivery to answer questions and address any other issues. Thereafter, they will continue to visit participating households on a monthly basis for 5 months to provide further advice and collect information on acceptability and use of the hardware.

The LifeStraw Family Filter (LSF) 2.0 is a second-generation of gravity-based water purifier that incorporates a chamber for safely storing treated water. The microbial barrier consists of a hollow-fibre filter that has been shown to meet the highest standards for microbiological performance and with regular maintenance and use to last for more than 18,000L (an estimated 3 years for a family of 5) (Clasen 2009). The first generation LSF has been shown in field studies to be highly effective in improving water quality and consistent (though not exclusive) use (Boisson 2010). However, the previous generation (hanging) model relied on householders to either treat their water every time they wanted to drink or to provide their own device to protect water from recontamination in the home. By integrating a safe storage vessel within the filter itself, and by reworking the device into a table-top design, the second generation device to be used in Rwanda is expected to reduce recontamination and increase use.

The Eco Zoom stove is based on the 'rocket' concept that uses an internal 'chimney' in the stove that directs air through the burning fuel (usually biomass), and encourages the mixing of gases and flame above it. Precise internal stove dimensions are used to achieve high combustion efficiency and transfer heat to the cooking pot. Comparison of improved cook stoves for USAID by the Berkeley Air Monitoring Group in Haiti, Uganda and Tanzania reported that the EcoZoom (aka StoveTek) stove saved 39% to 54% of fuel compared to open fires, cooked meals faster, and was the most preferred stove by 96% of households (USAID 2011). To date, however, the Eco Zoom filters have not been deployed widely in Rwanda. Studies suggest that the health, economic and environmental benefits of these technologies are most affected by their relative fuel costs, time and fuel use efficiencies, the incidence and cost-of-illness of acute respiratory illness, and the cost of household cooking time (Ezzati 2001; Smith 2000). The actual impact of the stoves on indoor air pollution and health will depend, among other things, on fuels used, cooking practices, quantities and other sources of indoor air pollution, time spent in close proximity to stoves, etc. (Smith 2011).

5. STUDY DESIGN

A household randomized controlled trial (RCT) to assess the impact of the intervention on drinking water quality and indoor air quality. These are discussed more fully in Sections 6-9 below.

6. STUDY SITES; STUDY POPULATION

The pilot involves the distribution of filters and cook stoves to all participating households in 2 or 3 villages in each of 11 designated Districts in Rwanda: Rutsiro, Karongi, Ngororero, Nyamasheke, Nyabihu Districts of Western Province (excluding part of the district to the north of the Ruhengeri road); Rubuvu District (excluding part of the district to the north of the Ruhengeri road); Nyaruguru, Nyamagabe, Muhanga, and Ruhango Districts in Southern Province; Gakenke District in Northern Province. These Districts have been identified as areas of need by MoH for improvements in drinking water and fuel conservation. With an average of 100 households per village, the pilot is designed to cover a total of 2000 households. Households will be eligible to participate in the study if they reside in selected villages and are willing to participate after receiving complete details regarding the study.

The proposed RCT will be limited to Karongi and Ngororero districts of Western Province selected for their proximity to Kigali. In order to conduct the RCT, DelAgua will recruit an additional 200 households from the overall pilot population in these two districts. A total of 400 households will participate in the RCT. Following a baseline survey, the households that agree to participate in the RCT after receiving complete details will be randomly allocated to either receive the intervention at the outset of the study (intervention group) or 5 months later after completion of follow up (control group).

9. Eligibility, Enrollment and Baseline; Sample Size.

In Karongi and Ngororero districts of Western Province, 400 households will be recruited to participate in a randomized, controlled trial (RCT) to assess the impact of the intervention on drinking water quality and indoor air quality. Households will be eligible to participate in the RCT if they meet the selection criteria for inclusion in the pilot rollout of the intervention (i.e., reside in a household in a village selected for the pilot) and agree to participate after receiving complete details in accordance with a prescribed information sheet.

Each household will be assigned a unique identification number for collecting and recording household data; no household members will be identified by name. Enrollment procedure and data collection will be administered by enumerators trained in research ethics and data collection methods by LSHTM staff. After a baseline survey that includes demographics, water management and cooking practices, half of the RCT households will be randomly allocated to an intervention group that will receive filters and stoves as part of the pilot. The remaining 200 households will be asked to continue their existing water management and cooking practices and will receive filters and stoves at the end of the 5-month follow-up period. The method of random allocation will be decided once context-specific data is gathered by speaking to key informants (i.e. village chief, MoH workers, villagers etc.).

The sample size for the RCT is based on detection of CO2 emissions from the improved cook stove as derived from previous field studies (USAID 2011). In order to observe a minimum of a 15% reduction in CO2 emissions (power=80%, p=5%), the intervention and control arms should have 173 households per arm. 200 households will be recruited per study arm in order to allow for any early termination, such as a household relocating to another Sector, or voluntarily leaving the study. Reassessment of the sample size will be conducted during the first months of data collection.

9.2 Follow-up Sampling and Surveillance.

Each RCT household will be visited (i) after initial community-wide delivery of the intervention, (ii) once 10-20 days after delivery of the intervention to address any issues, and (iii) thereafter each month for 5 months, giving a total of 7 household visits over the course of 6 months. During the monthly follow-up visits, the trained CHW will conduct a short survey addressing use and acceptability of the filter and cook stove. Once during the 6 month period, trained Environmental Health Officers (EHOs) will conduct a separate survey to (i) assess water management and cooking practices and (ii) record specific observations about the use of the filter and cook stove. These visits are conducted under the implementer’s direction for their own monitoring and evaluation purposes.

Independently, LSHTM-trained staff will conduct their own enrollment and baseline survey and will conduct monthly follow-up visits for the following five months to (i) uptake and consistent use, (ii) collect water samples from stored drinking water in the home. In addition, for those households randomly selected for air quality monitoring, UCB monitors will be placed in the participant’s home for 24 consecutive hours. Water samples will be assayed for thermotolerant coliforms (TTC), a WHO-prescribed indicator of faecal contamination. Air quality monitoring will assess the concentration of PM2.5 in the main cooking area as identified by the household.

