10. MEAUREMENT OF OUTCOMES

Outcomes of interest will be measured via a mixture of (i) survey questionnaire responses given by the household, (ii) observations made by enumerators, (iii) analysis of water samples and (iv) readings from instruments placed in the cooking area of participants for air quality.

The primary outcomes of this study are (i) to assess levels of faecal contamination (measured by thermotolerant coliforms, TTC) in stored water in the home that householders used for drinking, and (ii) to determine average 24-h concentrations of PM2.5 in the main cooking area as identified by participants. The secondary outcome of the study will be to assess the use of the filters and stoves based on self-report and spot-check observations.

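### The only sample-size statement is for CO2 emissions, which the trial neither measures nor lists as an outcome, so power for both primary outcomes is unstated

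*Protocol*

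**What the plan says.** The sample-size paragraph of the protocol (heading 9, Eligibility, Enrollment and Baseline; Sample Size) opens: "The sample size for the RCT is based on detection of CO2 emissions from the improved cook stove as derived from previous field studies". For a 15% reduction in CO2 emissions, with 80% power and a 5% level, it states that "the intervention and control arms should have 173 households per arm". It continues: "200 households will be recruited per study arm in order to allow for any early termination". It ends by promising to reassess the sample size in the first months of data collection, without naming an outcome, a variance estimate or a rule.

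Section 10 names the outcomes. It begins "The primary outcomes of this study are (i) to assess levels of faecal contamination", measured by TTC in stored drinking water, and gives the average 24-hour PM2.5 concentration in the main cooking area as the second primary outcome. Use of filters and stoves is the secondary outcome.

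Section 9.2 describes what the evaluation staff collect at monthly visits over five months: uptake and use, and stored-water samples for TTC. Air monitoring is restricted: "for those households randomly selected for air quality monitoring, UCB monitors will be placed" for 24 hours. The number selected is not given, and PM2.5 is the only pollutant named.

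**The concern.** A sample-size statement tells the reader what the trial can and cannot see on its own questions. Here it is tied to a quantity that the trial will not observe. Nothing in the objectives (Section 3), the outcomes (Section 10) or the data collection (Section 9.2) refers to CO2. The protocol also does not present CO2 as a stand-in for PM2.5. Section 4 says that the stoves' effect on indoor air depends on fuels, cooking practices and other pollution sources, so an emissions effect does not translate directly into kitchen PM2.5. It has no bearing on water quality.

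This is more than a detail left to an analysis plan. The protocol itself fixes the number recruited and gives the wrong quantity as the reason.

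The practical risk lies mainly with PM2.5. The pilot informs whether to proceed to large-scale delivery (Section 1). If a modest subset gave an inconclusive PM2.5 result, a reader who saw 80% power in the protocol could take it as evidence that the stove does not reduce exposure. The subset might not have been able to show a moderate reduction.

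**Working it through.** **Inputs from the protocol.** 15% reduction, 80% power, 5% level, 173 per arm, 200 per arm recruited, and 1:1 allocation ("half of the RCT households will be randomly allocated to an intervention group"). **Not given:** a mean, SD or CV for CO2; whether the 5% is one- or two-sided; any SD or target difference for TTC or PM2.5; the number of air-monitored households. Below I take the test as two-sided and the households as independent.

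**1. The protocol's own figure.** For two means with a common CV,

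n per arm = 2 × (1.960 + 0.842)² × CV² / 0.15².

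The squared term is 7.849. Solving n = 173 for the CV gives 0.15 × √(173 / 15.698) = 0.498. Forward, a CV of 0.50 gives 2 × 7.849 × 0.25 / 0.0225 = 174.4, so 175 per arm. The figure of 173 is therefore plausible for a CV near 0.50, but it cannot be verified because the protocol states no CV. A one-sided 5% test would imply a CV of 0.561. The step from 173 to 200 allows for 27/200 = 13.5% loss, since 173 / 0.865 = 200.

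**2. Does the figure carry over to the primary outcomes?**

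| | Sized on | Named as outcome | Measured | In whom |
|---|---|---|---|---|
| CO2 | yes | no | no | – |
| TTC | no | primary | yes, monthly | all RCT households |
| PM2.5 | no | primary | yes, 24 h | random subset, size not stated |

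It would carry over to PM2.5 only if PM2.5 had the same relative variability, the same target reduction and all households monitored. The protocol says none of the first two and contradicts the third.

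**3. TTC.** The standardised difference detectable with 80% power at 173 per arm, one sample per household, is 2.802 × √(2/173) = 0.30 SD. At an assumed log10 SD of 0.8 to 1.2 this is 0.24 to 0.36 log10, a ratio of geometric means of 10^0.24 = 1.7 to 10^0.36 = 2.3. Monthly samples can only improve on that.

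**4. PM2.5, as an illustration.** The CVs (0.5 and 1.0), the subset sizes and one measurement per household are assumptions. On the log scale, SD = √ln(1 + CV²), which is 0.472 and 0.833. The detectable reduction is 1 − exp(−d × SD), where d is the standardised difference detectable with 80% power by a two-sample t-test.

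| Monitored per arm | d | Log SD 0.472 | Log SD 0.833 |
|---|---|---|---|
| 30 | 0.736 | 29% | 46% |
| 50 | 0.566 | 23% | 38% |
| 100 | 0.398 | 17% | 28% |

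For example, at 50 per arm: 0.566 × 0.833 = 0.471, and 1 − exp(−0.471) = 38%.

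**The case against.** **The protocol makes no false claim about TTC or PM2.5.** This stands. The 80% is attached explicitly to CO2. A reader might infer that the trial claims a power it lacks for its own questions, or that it is underpowered. The text supports neither; what it shows is that the power for the primary outcomes is not stated.

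**One of the two primary outcomes looks well served.** This also stands. On step 3, TTC is probably amply sized, so the two outcomes should not be treated as equally at risk.

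**The PM2.5 figures rest on assumptions, and the scale matters.** This stands too. It is tempting to judge the subset by its power for a 15% reduction, but 15% is the CO2 target and the protocol sets no target for PM2.5. It is also tempting to work on the raw scale: at a CV of 1.0 the detectable reductions for 30, 50 and 100 per arm would then read 74%, 57% and 40%. That calculation keeps the SD equal in both arms, so a 74% reduction leaves a mean of 0.26 with an SD of 1.0, which is implausible for a concentration. On the log scale the same CV gives 46%, 38% and 28%. Section 11.2 does not fix the scale for PM2.5.

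**Sample size will be reassessed.** This mitigates only in part. It shows that 173 is not presented as final, but without an outcome or rule it does not supply the missing basis, and the only quantity it could refer to as written is not measured.

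**Assumed SDs, repeats and subset size could sit in an analysis plan.** Their absence alone would not be a finding. The CO2 basis is an error in the protocol's own text.

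**The roll-out will not turn on this result alone.** Correct: Section 12.3 makes the campaign subject to conditions and also draws on the larger evaluation. This limits the consequence but leaves the mismatch.

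**Conclusion.** The point holds as a mismatch inside the protocol. The sole power statement concerns a quantity that is neither an outcome nor measured, so it applies to neither primary outcome, and 173 per arm cannot be the PM2.5 denominator.

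The documents do not show that the trial is too small. With one sample per household, 173 per arm detects 0.30 SD, probably ample for log10 TTC. For PM2.5 the answer depends on a subset size and a variability that the protocol does not give. Under the assumed log-scale SDs of 0.47 to 0.83 and one measurement per household, the detectable reduction runs from about 17-28% at 100 per arm to 29-46% at 30 per arm. These ranges illustrate what is at stake; they do not estimate the trial's actual power. The statement should be corrected because it concerns both primary outcomes and the correction is cheap.

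**What to change.** Rewrite the sample-size paragraph:

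- Remove the CO2 reduction as the basis for power.
- For log10 TTC, state the power or detectable difference with the planned 200 per arm and its loss allowance, the assumed SD, and how the monthly samples enter.
- For log PM2.5, fix the number of monitored households per arm and state the assumed SD and the reduction detectable with 80% power. If a target reduction is set, justify it for PM2.5 rather than carrying over 15% from CO2.
- Say that the planned reassessment of sample size, including the number of monitored households, will use the variability of these two outcomes.

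The cost is one paragraph, plus a decision on the number of monitored households. The correction does not itself call for more households. The drawback is that the stated PM2.5 precision may look less favourable than the present 80% for 15%.

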10. MEAUREMENT OF OUTCOMES

Outcomes of interest will be measured via a mixture of (i) survey questionnaire responses given by the household, (ii) observations made by enumerators, (iii) analysis of water samples and (iv) readings from instruments placed in the cooking area of participants for air quality.

The primary outcomes of this study are (i) to assess levels of faecal contamination (measured by thermotolerant coliforms, TTC) in stored water in the home that householders used for drinking, and (ii) to determine average 24-h concentrations of PM2.5 in the main cooking area as identified by participants. The secondary outcome of the study will be to assess the use of the filters and stoves based on self-report and spot-check observations.

11. DATA ENTRY AND MANAGEMENT; DATA ANALYSIS

11.1 Data Entry and Management. Data will be collected using prescribed survey tools on password-protected smartphones, encrypted and transmitted securely to a password protected database.

11.2 Data Analysis. The data will be validated by checking for completeness, consistency, and data recording errors. Stata Version 11.0 (Stata Corporation, College Station, Texas, US) will be used for analysis, including comparisons of intervention and control households using the t-test and the Wilcoxon test (where appropriate) for continuous outcomes, and the Fisher’s exact test or the Chi-square test for binary outcomes. Generalized estimating equations or random effects models will be used for the analysis of binary outcomes to control for repeated measurements at the same household. Statistical analyses of microbiological data areconducted after log10 transformation of TTC count values to account for the skewed distribution.

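### Section 11.2 names a repeated-measures method only for binary outcomes and does not say how the monthly log10 TTC values, a continuous primary outcome, are combined within a household

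*Protocol*

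**What the plan says.** Section 10 makes TTC one of two primary outcomes: the aim is "to assess levels of faecal contamination (measured by thermotolerant coliforms, TTC) in stored water in the home". Under Section 9.2, the independent evaluation staff "will conduct monthly follow-up visits for the following five months" and at those visits "collect water samples from stored drinking water in the home". A household can therefore contribute up to five follow-up TTC values.

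Section 11.2 analyses them "after log10 transformation of TTC count values to account for the skewed distribution", that is, as a continuous variable. The same section compares the households of the two arms "using the t-test and the Wilcoxon test (where appropriate) for continuous outcomes", with Fisher's exact or Chi-square tests for binary outcomes. It then adds that "Generalized estimating equations or random effects models will be used for the analysis of binary outcomes to control for repeated measurements" within a household.

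Section 3, objective (ii), asks for the impact on water quality across the whole five months. No section defines a mean over visits, a single analysis visit or a longitudinal model for log10 TTC.

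**The concern.** The authors saw that repeated values from one household are not independent and named a remedy, but attached it to binary outcomes only. The water-quality primary outcome, on the scale the protocol chooses for it, falls outside that remedy and under the two-sample tests.

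Those tests assume independent observations. Repeated samples from one household share a source, storage habits and filter use, and are likely to be positively correlated. If all visit-level values are pooled, the standard error is too small, the p-value too low and the confidence interval too narrow. This would affect both the test and the reported size of the effect on a primary outcome, and Section 12.3 says the results inform the decision on the full-scale campaign.

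**Working it through.** **No figure in the plan to reproduce for this point.** The protocol gives no power, variance or correlation for TTC. Its one sample size calculation concerns CO2 emissions: "the intervention and control arms should have 173 households per arm", with 200 recruited. It states no standard deviation and has no repeated-measures term, so it can be neither confirmed nor refuted, and nothing below depends on it.

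**Inputs**
- Follow-up samples per household: m = 5 (Section 9.2).
- Households per arm: 200 (Section 9), so at most 200 × 5 = 1000 samples per arm. With the 173 per arm that the sample size requires, it would be 173 × 5 = 865.
- Within-household correlation of log10 TTC (ICC): not given. Assumed range 0.05 to 0.6, with 0.1, 0.3 and 0.5 as the main cases.

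**Formulas, if visit-level values are treated as independent**
- Design effect DE = 1 + (m − 1) × ICC = 1 + 4 × ICC.
- Reported standard error as a fraction of the correct one = 1/√DE.
- Actual two-sided type I error = 2 × [1 − Φ(1.96/√DE)].
- Actual coverage of the nominal 95% interval = 1 minus that value.
- Effective independent samples per arm = 1000/DE.

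Example at ICC 0.3: DE = 1 + 4 × 0.3 = 2.2; 1.96/√2.2 = 1.32; type I error = 2 × [1 − Φ(1.32)] ≈ 18.6%.

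| Assumed ICC | DE | SE fraction | Type I error | 95% CI coverage | Effective samples per arm |
|---|---|---|---|---|---|
| 0.05 | 1.2 | 0.91 | 7.4% | 92.6% | 833 |
| 0.1 | 1.4 | 0.85 | 9.8% | 90.2% | 714 |
| 0.3 | 2.2 | 0.67 | 18.6% | 81.4% | 455 |
| 0.5 | 3.0 | 0.58 | 25.8% | 74.2% | 333 |
| 0.6 | 3.4 | 0.54 | 28.8% | 71.2% | 294 |

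The type I error depends on m and the ICC, not on the number of households, so losing households does not change it. Missed visits reduce it somewhat: with four samples per household at ICC 0.3, DE = 1 + 3 × 0.3 = 1.9 and the error is about 15.5%.

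**Check by simulation** (no true effect, 200 households per arm, 5 visits, 4000 runs per ICC), percentage of runs with p < 0.05:

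| Assumed ICC | t-test, pooled samples | Wilcoxon, pooled samples | t-test on household means |
|---|---|---|---|
| 0.1 | 10.3% | 9.9% | 5.1% |
| 0.3 | 18.3% | 17.2% | 4.8% |
| 0.5 | 25.2% | 24.4% | 4.5% |

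The simulation agrees with the formula. Choosing the Wilcoxon test does not remove the problem, whereas reducing each household to one mean does.

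**The case against.** The strongest reply is that Section 11.2 speaks of comparing households, not samples. A t-test on each household's mean log10 TTC fits that sentence, answers objective (ii) with one estimate and keeps its error rate, as the last column of the simulation shows. The list of tests is also introduced as non-exhaustive, the TTC sentence itself names only a transformation, and authors who mention repeated values within a household are unlikely to pool them naively.

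Much of this stands. A reader might infer that the protocol prescribes an invalid test, or that the TTC result has the wrong error rate however the text is followed. The document does not support either claim, because the household-mean reading is open and valid. A reader might also infer that five separate visit tests inflate the false-positive risk. That requires a rule that any one significant visit counts as success, and the protocol states no such rule.

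What does not stand is that the household wording settles the matter. The same sentence covers binary outcomes, and for those the authors still found it necessary to add GEE or random effects. Nor is this a detail simply left to a statistical analysis plan. The protocol assigns methods by type of outcome, and a plan that follows the assignment would carry the gap forward.

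**Conclusion.** The point holds as a gap in a stated assignment of methods: a longitudinal method is named for binary outcomes, and none is named for a continuous primary outcome measured up to five times per household. Confidence in that reading is high.

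The error rates are conditional. A type I error of about 10%, 19% or 26% requires that visit-level values be pooled as independent, that all five samples be available, and that the within-household correlation be 0.1, 0.3 or 0.5, values the protocol does not give. Under a household-mean analysis the error stays near 5%.

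The point is confined to TTC. Section 9.2 does not make clear whether a household selected for PM2.5 monitoring is measured once or repeatedly, so nothing is claimed for that outcome.

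**What to change.** Either of two changes to Section 11.2 is enough.

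1. Extend the GEE or random effects sentence from binary outcomes to all outcomes measured more than once per household. Log10 TTC is then analysed with one linear mixed model or GEE, with household as the cluster and arm and visit as fixed effects. The primary estimate is the arm difference averaged over the follow-up visits.
2. Alternatively, state that the t-test or Wilcoxon test is applied to each household's mean log10 TTC over follow-up.

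The first uses incomplete households more naturally; the second is simpler and adequate when follow-up is nearly complete. Apply the same rule to PM2.5 only if a household is monitored more than once.

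The cost is one sentence, written before the data are analysed. No new data, visits or software are needed, since the protocol already plans models of this class for binary outcomes.
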